### Weekly intervention evaluation notes by case managers

Throughout the 12-week intervention period, CMs are required to complete and submit a digital weekly intervention evaluation note to the project coordinator and principal investigator for regular review (Table 1). This process ensures that the structured intervention is delivered in accordance with the established protocol.

**Table 1 Tab1:** The details of intervention evaluation notes by case managers

**Question**	**Details**
1.	Whether the weekly tele-counseling occurred outside the scheduled program
2.	The purpose of the counseling session
3.	Any health professionals or other individuals involved
4.	A record of which intervention components were discussed and reviewed
5.	Capture enablers and barriers to program implementation, troubleshooting issues related to the eHealth system
6.	Whether the recommendations were practiced, and the reasons for any failure to follow the advice
7.	The status of the participant's problems will be documented
8.	Whether these issues have worsened or improved since the beginning of the intervention, along with an assessment of the extent of any changes

### Intervention protocol

The intervention protocol is reported based on Template for Intervention Description and Replication (TIDieR) checklist and guide [79]. Prior to the commencement of the 12-week intervention, a two-day workshop will be conducted to introduce five key domains: (1) health risk appraisal and self-care; (2) PA and self-administrated acupressure; (3) emotion and stress management; (4) WFPB diet, nutrition, and disease relationships; and (5) meditation and mindfulness practices. This workshop is led by a multidisciplinary team comprising the principal investigator, registered TCM practitioner, senior physiotherapist (SPT), fitness trainer, registered dietitian, mindfulness instructor, senior registered nurse, and WFPB medical doctor. CMs are required to attend the workshop to familiarize themselves with the intervention content and the operations of the eHealth system. On the final half-day of the workshop, the eHealth system will be distributed to all EG participants. A briefing and hands-on training session will be organized by the information technology provider and technicians to demonstrate the operation of the eHealth system. All EG participants will be guided to learn self-monitoring logbooks to record their WFPB diet, physical exercise, mindfulness practices and a stress management logbook during the joint training and demonstration. An e2HLE booklet will be provided to all EG participants, encompassing a range of topics (Table 2).

**Table 2 Tab2:** The details of the e2HLE booklet

**Component**	**Details**
PA and self-administrated acupressure	-The importance and key points of PA; warm-up exercise, stretching, balance training, muscle strength training, aerobic exercise, cool down exercise with photos, URL links and QR codes. -The origin, efficacy and operating techniques of acupressure and self-administrated acupressure methods for the twelve most common acupressure points (e.g., GV20 Baihui, GB20 Fengchi, GB21 Jianjing, BL52 Zhishi, LI10 Shousanli, ST36 Zusanli, LI4 Hegu, SP6 Sanyinjiao, BL40 Weizhong, KI1 Yongquan, etc.)
Meditation and mindfulness	-The theory, origin and scientific evidence of mindfulness; how meditation improves physical and mental health; meditation while walking, standing, sitting or lying down; understanding autopilot and its relationship to stress; be aware of distractions and stress and use your breath as an anchor; practice observing brain wave changes during breathing; how to practice mindfulness at home; apply what you have learned to re-energize your life; be kind to yourself; in times of stress, pause, breathe, and pour loving kindness into yourself; wise actions when stress rises; and meditation practice in life. -Mindfulness applications with QR codes (e.g., Pause and Breathe, Newlife 330, Mindful Flourishing, and Jockey Club "Peace and Awareness").
WFPB diets	-The concept of a whole food plant-based (WFPB) diet, common vegetarian traps, important sources of nutrients for vegetarians, holistic vegetarianism and disease, introduction to special vegetarian ingredients, WFPB recipes, and handling of ingredients. -Featuring WFPB plan and recipes for preparing meals, soups, snacks, and smoothies to be consumed throughout the week. The WFPB dietary plan is designed to provide appropriate levels of plant-based proteins, carbohydrates, and fats, along with essential nutritional components (e.g., vitamins and minerals) to support optimal health.

On the day of the intervention, CMs will provide approximately 30 min of counseling to all EG participants. They will be advised to gradually modify their dietary habits and establish a weekly routine that incorporates six designated exercise videos or other preferred physical activities, performed at a moderate-to-vigorous intensity for a minimum of 30 min per day, five days a week. Additionally, EG participants will receive guidance on self-administrated acupressure techniques, utilizing video clips that demonstrate the most common acupressure points, compiled by the TCM practitioner and SPT. Participants will also be instructed on how to use four meditation applications that are integrated into the eHealth system for meditation and mindfulness practices, allowing them to engage with these resources as needed.

EG: All EG participants will continue their prescribed medical treatments, if applicable. Throughout the 12-week intervention, participants will monitor their health vitals weekly and complete daily self-monitoring logbooks to record their WFPB diets, PA, and mindfulness practices. Table 3 presents the 12-week intervention sessions with three main components: (1) WFPB diet, (2) PA and self-administrated acupressure, and (3) meditation and mindfulness practices. They are required to attend nine weekly theme-based sessions. Each component consists of three sessions, with each session lasting 120 min. Additionally, there will be three process evaluation sharing sessions conducted in a focus group format, each lasting 60 min, resulting in a total of twelve sessions. During the weekly theme-based sessions, the WFPB diet component will cover various topics. Additional WFPB dietary consultation sessions with a registered dietitian can be arranged upon participant request throughout the entire intervention period. Regarding PA and self-administrated acupressure, EG participants will receive hands-on training in both physical exercise and fundamental self-acupressure techniques. Participants will also be encouraged to incorporate additional physical exercises into their routines as they progress. In the sessions related to meditation and mindfulness, various skills and techniques will be taught, as presented in Table 3.

**Table 3 Tab3:** The 12-week intervention sessions with three main componentsThe 12-week intervention sessions with three main components

**12-session**	**Weekly theme-based sessions and process evaluation sharing sessions**
Sessions 1, Session 5, Session 9	**Component 1: WFPB diet ** Knowledge and evidence-based research of whole plant-based foods (i.e. whole grains, beans, legumes, fruits, vegetables, sea vegetables, seeds and nuts) along with rainbow colors, nutrition and disease relationships, reading food labels, healthy cooking methods, food preparation and storage, identifying common food traps, and avoiding animal-based and unhealthy foods (e.g. meats, milk, dairy products, eggs, refined carbohydrate, instant and convenient foods, processed and ultra-processed foods, intimation meats and vegetables, foods and sauces high in sodium, free sugar, trans-fats and saturated fats, leftovers, overcooked and deep-fried foods, double-stewed soup, shortening, margarine, palm and refined oils, Chinese sausage, salted fish and egg, fermented bean curd, sweet pastry and commercial beverages, alcohols, etc.). Calculate daily total energy intake and appropriate levels of macronutrients from non-animal sources, including carbohydrates, fats, and proteins, using the caloric application. Emphasize the consumption of whole plant-based foods, aligning with the basic tips to practice “Two Plus Three Every Day” – at least two servings of fruits and three servings of vegetables (https://www.chp.gov.hk/en/static/100011.html), as well as the importance of diet quality, dietary fiber, mono- and polyunsaturated fatty acids, polyphenols, phytochemicals, antioxidants, plant-based protein sources and fatty acids, and micronutrients (e.g., vitamin B12, vitamin D, potassium, iron, calcium etc.), along with maintaining adequate water and fluid intake. Problem-solving strategies for eating out and managing sickness during the intervention. Providing evidence-based WFBP video materials and sharing relevant meal preparation video clips. Cooking demonstrations will also be included and presented by a dietician.
Session 2, Session 6, Session 10	**Component 2: PA and self-administrated acupressure** Coach EG participants in performing exercises correctly. Coach to perform self-administrated acupressure correctly. Encourage to perform and retain any other preferred physical activities, such as brisk walking, swimming, yoga, badminton, Chinese dance, Tai Chi, or Qigong, etc. Instruct using exercise and acupressure videos, and emphasize the importance of wearing appropriate athletic attire and footwear to minimize the risk of injury.
Session 3, Session 7, Session 11	**Component 3: Meditation and mindfulness** Include inner climate examination, body scans, mindful stretching, and attentive eating practices. Include creating a meditation bottle, introducing a seven-step self-stabilization practice, identifying nine types of thought traps, and performing ten-finger gratitude exercises. Experience sound navigation, sensory exploration, and musical notes associated with hot springs.Demonstrate using four mindfulness applications.
Session 4, Session 8, Session 12	**Process evaluation sharing sessions** Discuss any barriers and facilitators they encountered related to intervention components; identify strategies for refining the intervention process; share their perspectives on enablers, and challenges encountered while using the eHealth system, including reasons for not achieving the expected weight loss.

EG participants’ family members, helpers or friends are invited to attend the theme-based sessions as observers or supporters at no cost, provided they give written informed consent. They may also assist participants who require support with digital literacy. Comprehensive step-by-step guides, hands-on training sessions, helpdesks, and dedicated IT staff will be available to assist with any digital challenges that may arise. This component is aligned with a “buddy-assisted health coaching approach” that enhances participant motivation and adherence to health-related behaviors, as encouragement from buddies can foster a sense of accountability and commitment to lifestyle changes. During the intervention, EG participants will have access to educational materials, videos, and meditation applications and maintain self-monitoring logbooks through the eHealth system.

During the process evaluation sharing sessions, EG participants will be organized into small groups of approximately 10 to 12 individuals (Table 3). Weekly individualized tele-counseling sessions by CMs, each lasting approximately 30 min, will be conducted. These sessions aim to increase motivation, review personalized care plans, and provide general support in making goal-based lifestyle changes and addressing challenges. Mutual support networking will be facilitated regularly between CMs and participants through WhatsApp or telephone communication. Each EG participant will receive a supermarket gift card valued at HKD200 (approximately USD25) as reimbursement for their time and registration fees, as well as an incentive for completing the 12-week intervention and participating in data collection.

WLCG: Participants will receive usual care from the elderly centers for the first three months. For ethical reasons, those in WLCG will crossover to the intervention arm after 12 weeks, receiving the same intervention content, dosage, and duration as the EG participants.

After completing stage one, all participants will attend a swearing-in ceremony where selected individuals will become “Smart Healthy Aging” ambassadors, coaching participants in stage two. This approach follows the Train-the-Trainer (TTT) model [80] and incorporates health coaching [69]. Key trained participants will share their insights, provide ongoing support to new participants, and facilitate the intervention process to build confidence and competence. They will receive a certificate of appreciation during the ceremony. The entire implementation process will be videotaped to create non-commercial documentary clips that aim to synthesize and disseminate evidence on the effectiveness of community-based behavior change interventions to a wider audience.

The evaluation of e2HLE is grounded in a whole-systems approach and examines three levels of the system: (i) the individual participant at the micro system level, focusing on effectiveness, process, implementation, and outcomes; (ii) the site or region at the meso system level, which considers the program context; and (iii) the overall program at the macro system level, assessing the potential for program sustainability at the organizational and/funder levels. In addition to focusing on the micro level, which examines individual participants, qualitative assessments will be conducted with CMs, experts as well as the project coordinator and social services department manager, to evaluate the meso and macro levels after the completion of both stages.

### Procedure of data collection

Eligible participants will be invited to join the study after providing signed consent following a detailed explanation of the study’s purpose and procedures. Baseline data (T1) will be collected by trained assessors. After the 12-week intervention, assessors who are blinded to group allocations will conduct physical assessments. Participants will complete questionnaire surveys, including health examinations, using a secure institutional account in Qualtrics to ensure data privacy. They will fill out the baseline questionnaire and health examination before randomization and participate in a follow-up interview approximately three months later (T2). A structured questionnaire will collect data, with only demographic information gathered at T1, and all measurements will be administered in Cantonese, consistent with previous Hong Kong studies. Appendix C details the outcome measures, assessment methods, and psychometric information.

### The primary outcome

Body weight will be measured using the same electronic weight scale in the community center.

### Secondary outcomes

The score range, direction and psychometric details of the secondary outcomes are presented in Appendix C. The secondary outcomes include enhancements in IC, specifically targeting four domains: motor function, vitality (nutrition), psychological well-being, and mental and cardiac health facilitated by the eHealth system. Additionally, improvements are anticipated in at least two of the cardio-metabolic risk factor profiles, including waist circumference, blood pressure, BMI, visceral fat, HbA1c, LDL cholesterol levels, and homocysteine (assessed through blood tests). Other expected outcomes encompass improved sleep quality and reduced chronic pain, decreased depressive symptoms and stress levels, and enhanced self-care capacity and social support.

### Pre- and post- blood tests

A total of 20 ml of blood will be drawn and tested by medical professionals in a designated laboratory. The blood tests will cover five main categories: (1) Albumin (nutritional marker); (2) CRP (inflammation marker); (3) Total blood cell count, creatinine, BUN, liver function tests, blood sugar levels, and HbA1c (indicators of anemia, diabetes, and organ function); (4) Total cholesterol, HDL, and LDL levels (cardiovascular disease risk factors); and (5) Homocysteine (indicating potential vitamin B-12 or folate deficiency). Individualized sessions lasting 15 to 20 min will be held for all EG participants after receiving their pretest and posttest blood reports, approximately 2 to 3 weeks after the intervention starts and ends. During these sessions, a registered dietitian and/or a WFPB medical doctor will provide explanations and advice for follow-up care. If any blood test results are abnormal, appropriate referrals for further treatment will be recommended.

### Mediators

This study hypothesizes that weight loss and its secondary outcomes are mediated by several factors, including self-efficacy, digital health literacy, mindfulness, and gerotranscendence. These elements collectively enhance an individual’s ability to adopt and maintain healthy behaviors. Higher self-efficacy helps individuals overcome obstacles and stay committed to weight loss goals. Digital health literacy is crucial in today’s tech-driven healthcare, enabling effective access to online health information and resources for informed decision-making. Mindfulness promotes awareness of thoughts and feelings related to food and body image, fostering healthier eating and emotional regulation. Gerotranscendence reflects a shift in perspective in older age, motivating individuals to prioritize their health. Together, these variables create a supportive framework that increases the likelihood of successful weight loss by addressing both psychological and practical aspects of behavior change (Fig. 1).

### Validity and reliability

All the selected measures demonstrated good reliability with Cronbach’s alpha >0.7 in past samples with local older adults and have been adopted for the local or Chinese context. For example, the Chinese version of the Pittsburgh Sleep Quality Index (CPSQI) is a reliable and valid instrument to assess subjective sleep quality. The CPSQI showed acceptable test-retest reliability with a coefficient of 0.85 for all subjects and 0.77 for primary insomniacs [81]. The General Self-Efficacy scale is commonly used to measure behaviors related to motivation, self-esteem, mental health, general well-being, and quality of life. The scale has demonstrated good internal consistency (α = 0.91) and criterion validity, making it suitable for investigating self-efficacy related issues in the Chinese population [82]. Any difference in baseline characteristics between groups will be accounted for in the statistical analysis.

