**Methods:**

A waitlist randomized controlled trial featuring two parallel arms—an experimental group (EG) and a waitlist control group (WLCG)—will recruit 150 participants aged 60 and older with MetS and psychosomatic symptoms from five elderly centers. Participants will be randomly assigned to either the EG or WLCG. The 12-week intervention comprises weekly theme-based sessions focused on self-care, whole food plant-based diets, physical activity, self-administered acupressure, and mindfulness practices. These components are supported by an eHealth system that offers educational materials and facilitates self-monitoring of bio-signals and lifestyle changes, along with a comprehensive booklet. A two-day workshop supported by a multidisciplinary team will be conducted prior to the intervention. The intervention strategies utilize a combination of modules, incorporating in-person individual and group meetings, tele-counseling, technology-driven support groups, and buddy-assisted health coaching. A mixed-methods approach will be employed, with EG participants undergoing pretest and posttest assessments through surveys, health examinations, and blood tests, supplemented by qualitative process evaluations. WLCG participants will receive usual care for the first three months before cross over to the intervention arm. Data will be collected between baseline and the 12-week follow-up, with quantitative analysis conducted using SPSS and generalized estimating equations models.

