### Planned data analysis

Data will be entered and analyzed using SPSS version 30. Demographic data will be summarized, with frequency and percentage for categorical variables, and mean and SD for continuous variables. Group difference at baseline will be compared using chi-squared tests for categorical variables and ANOVA for continuous variables. The Pearson correlation will be used to explore the relationship between weight loss and adherence scores. Changes in variables between baseline and the three-month follow-up will be compared using paired t-tests or Wilcoxon signed-rank tests as appropriate. To compare the mean changes in the continuous outcome variables including body weight, waist circumference, BMI, HRV and HRR, sleep quality, nutritional status, self-care capacity, perceived depressive symptoms and stress level, chronic pain among the two groups with the intention-to-treat principle. This approach ensures that all participants are included in the analysis as originally assigned, regardless of their level of compliance, thereby mitigating the impact of missing data. For missing values, methods like multiple imputation and sensitivity analyses will test the robustness of results. Adherence rates will also be analyzed alongside outcomes, using generalized estimating equations to account for repeated measures and reliably estimate intervention effects. Medication use for metabolic diseases and psychosomatic symptoms will be documented at baseline and follow-up, serving as a covariate in analyses to distinguish intervention effects. Subgroup analyses may compare outcomes between medicated and non-medicated participants. As age may significantly influence participants’ responsiveness to the intervention, conducting subgroup analyses by age cohort offers more specific insights into how the intervention may benefit older adults at different stages of aging. Post hoc pairwise comparisons of the changes in the outcome variables across the two study groups will be performed to compare the effectiveness of the EG and the WLCG. All the tests are two-sided and a *p* < 0.05 will be considered statistically significant.

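### The plan adjusts for whatever baseline differences appear, so the covariates in the body-weight analysis depend on chance imbalance instead of one pre-stated between-arm model

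*Protocol article*

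**What the plan says.** The Validity and reliability section of the protocol article ends with a covariate rule: "Any difference in baseline characteristics between groups will be accounted for in the statistical analysis". It gives no list, threshold or model.

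Planned data analysis contains the following:

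- Baseline tests: "Group difference at baseline will be compared using chi-squared tests for categorical variables and ANOVA for continuous variables".
- Tests of change over time: "Changes in variables between baseline and the three-month follow-up will be compared using paired t-tests or Wilcoxon signed-rank tests as appropriate".
- A between-group comparison of mean changes, with body weight first in its list, ending "chronic pain among the two groups with the intention-to-treat principle". The sentence has no main verb and names no method.
- Generalized estimating equations (GEE), in a sentence that opens with adherence rates: "using generalized estimating equations to account for repeated measures and reliably estimate intervention effects". The abstract is broader: "quantitative analysis conducted using SPSS and generalized estimating equations models".
- The contrast of the experimental group (EG) with the waitlist control group (WLCG): "Post hoc pairwise comparisons of the changes in the outcome variables across the two study groups will be performed".
- One covariate named in advance, medication use, which "will be documented at baseline and follow-up, serving as a covariate in analyses to distinguish intervention effects".

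The section on randomization states that allocation is done at each elderly centre and that people sharing a household are randomised together.

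**The concern.** After proper randomisation, a baseline difference between arms is a chance event. A rule that adjusts for whatever differs leaves the adjusted model unknown until the data are seen. It also selects on the wrong property: a variable deserves adjustment because it predicts the outcome, whether or not it happens to be imbalanced. Two analysts following the rule could reach different covariate sets and different estimates for body weight.

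Three features of the same plan add to this.

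- The between-arm comparison is of changes, and the contrast that answers the trial's question is labelled post hoc. Within-arm paired tests stand beside it, and nothing says which result decides.
- Medication is recorded at both visits, and the text does not say which value enters the model. The follow-up value arises after randomisation and could be affected by the intervention, so adjusting for it could remove part of the effect.
- An unshown analysis plan could add model terms, but it would have to contradict the any-difference rule rather than complete it.

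**Working it through.** **Inputs from the article (Sample size).** Effect size 0.5, power 80%, two-sided alpha 0.05, 126 inflated to 140, 8% attrition, 75 recruited per arm. **Assumed, because the article does not give them:** the number of baseline variables tested, and the correlation r between baseline and follow-up.

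**1. Reproducing the plan's own sizing.**
- Per arm: 2(1.96 + 0.84)² / 0.5² = 62.8, so 63, or 126 in total.
- 126 / (1 − 0.10) = 140.
- 140 / (1 − 0.08) = 152.2, so 153, against 150 stated. This is close enough.
- Completers: 75 × 0.92 = 69 per arm, giving about 84% power.

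The sizing is therefore an unadjusted two-arm comparison.

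**2. How often chance alone triggers the rule, if a difference means p<0.05.** For k independent baseline variables, P(at least one) = 1 − 0.95^k.

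| k (assumed) | P(at least one p<0.05) |
|---|---|
| 5 | 23% |
| 10 | 40% |
| 20 | 64% |

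The trial collects demographics, body measures, a five-category blood panel and many scales, so values of k in this range are plausible. Correlation among the variables would generally lower these figures.

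**3. Effect on the test, in one simple case.** The simulation used 20,000 trials with no effect and 69 per arm. Follow-up weight was adjusted for baseline weight only when the baseline test was significant.

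| r | True alpha, conditional adjustment | True alpha, always adjusted |
|---|---|---|
| 0.5 | 0.044 | 0.050 |
| 0.7 | 0.035 | 0.048 |
| 0.9 | 0.022 | 0.049 |

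The error here is conservative. The case concerns follow-up weight; an unconditional comparison of changes also held about 0.05. Free choice among several covariates was not simulated, so no inflation is claimed.

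**4. Precision of baseline adjustment against change scores.** With equal variances, the change score has variance 2(1 − r)σ² and the baseline-adjusted analysis (1 − r²)σ². The ratio is (1 + r)/2.

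| r (assumed) | Ratio | Equivalent extra participants (1/ratio − 1) |
|---|---|---|
| 0.5 (questionnaire) | 0.75 | 33% |
| 0.7 (questionnaire) | 0.85 | 18% |
| 0.95 (weight) | 0.975 | about 2.5% |

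**5. Does the fix need more people?** With 69 completers per arm and d = 0.5 on the change-score SD, the SD is multiplied by √((1 + r)/2). Power is then 95%, 92%, 89% and 85% at r = 0.3, 0.5, 0.7 and 0.9, against 84% unadjusted. Household clustering is left out of both sides of this comparison.

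**6. Why the paired tests need a label.** Suppose both arms change equally, by δ SDs of change (assumed). Then P(EG significant) = Φ(δ√69 − 1.96), which is 0.38 at δ = 0.2 and 0.70 at δ = 0.3. P(EG significant and WLCG not) = P(1 − P), which is 0.24 and 0.21, with a maximum of 0.25 between them. A two-sided 5% between-arm test would favour EG in 2.5%.

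**The case against.** A reader might infer that paired within-arm tests take the place of any comparison between arms. The article does not support that. It plans an intention-to-treat comparison of mean changes that includes body weight, GEE to estimate intervention effects, and an EG versus WLCG comparison. The abstract names GEE, and the sample size is that of a two-arm comparison. It follows that the 21% to 25% in step 6 is not an error rate of this trial. It would become one only if effectiveness were judged from the paired tests, and no section says so. What remains is that the order of priority is unstated and that the key contrast is called post hoc.

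Other objections have weight:

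- The article does not link the baseline tests to covariate choice. The two sentences stand in different sections, and joining them is an inference. The rule is nonetheless open-ended without the tests, since it covers any difference observed.
- A comparison of changes is valid under randomisation and uses the baseline value, as would a GEE on both visits. Adjusting for baseline improves efficiency; it does not correct a bias, and for weight the gain is small.
- An article may leave model terms to an analysis plan. The absence of a covariate list is therefore not the finding. The finding is the rule that the article states.
- A plain analysis of covariance would ignore the randomisation of households as units. This is correct, and the fix allows for it.

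**Conclusion.** The point stands as a correction that should be made, not as a flaw that invalidates the trial. The article commits the analysis to covariates that depend on chance imbalance, and it plans significance tests of arms that were randomised. On assumed counts of 5 to 20 independent variables, and reading a difference as p<0.05, chance alone would trigger adjustment in 23% to 64% of trials. The resulting shift in the weight estimate cannot be computed from the article. The one simulated case gave a conservative test, and inflation is not shown.

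The unranked paired tests, the post hoc label and the unspecified timing of the medication covariate are weaknesses of wording in a plan that does compare the arms. Precision is a secondary argument: about 2.5% for weight at r = 0.95, and the equivalent of 18% to 33% more participants for questionnaires at r = 0.7 to 0.5, all with r assumed. For the primary outcome the benefit is an estimate fixed in advance.

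**What to change.** 1. Replace the any-difference rule with one between-arm model for 12-week body weight, named as the primary test. Regress the T2 value on arm, baseline weight, centre and a short fixed list of baseline covariates. Fit it by GEE, or by analysis of covariance, with household as the cluster in either case.
2. In that list, use medication as recorded at baseline only.
3. Reuse the model for the other continuous outcomes, each with its own baseline value.
4. Drop baseline significance tests as a basis for choosing covariates; a descriptive baseline table is enough.
5. Remove the post hoc label from the EG versus WLCG contrast, and label paired within-arm results descriptive.

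The cost is wording, settled before outcome data are examined. Baseline values and medication are already to be collected, and centre and household are known from the design. The recruitment target does not change.
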